### Data collection

Consent and all study data will be collected electronically using a secure online system, the ‘ASSISTANT’ system (https://studyassistant.org.uk/). It combines a secure purpose-built study website database designed by Baseline Software Ltd (East Sussex, UK) (https://TIPTOE.org.uk/) and utilises REDCap [46, 47], hosted by Cardiff University, as a data repository. All data entered by participants (or the trial team when support is required) are thus stored confidentially, only accessible to the central trial team and allocated site staff. The study website has built-in validations to promote data quality, e.g. double data entry, range checks, missing data, etc. which have been extensively tested.

### Expression of interest and consent

Potential participants identified by TIPTOE sites or through responding to advertisements will be directed to the TIPTOE website (see ‘Data collection’ section for overview of website). The TIPTOE website contains summary, pictorial and detailed Participant Information Sheets (PIS). Interested individuals are invited to complete the expression of interest (EOI) form within the website. This form will collect individuals’ name, age, contact details and eligibility information. The website will automatically determine whether potential participants are eligible. If there are any queries, the central trial team may call potential participants to check eligibility. Personalised emails will be sent in response to all EOIs to thank them for their interest and inform them, based on the information they have provided, whether they are eligible to take part in the trial or not. Eligible participants who can be allocated to a TIPTOE research site will be sent a secure link via email to complete the consent form.

If those interested in taking part are unable or unwilling to use the study website, local advertisements will contain a central telephone number to contact the central trial team, who will provide support in completing the EOI and consent forms. Alternatively, potential participants identified by a TIPTOE site can consent in person with a delegated member of the team at the site. Potential participants are also encouraged to join the trial with a nominated supporter (e.g. friend, family member or carer) who can support them in using the study website.

Following initial provision of informed consent, participants with MLTCs such as dementia may experience a decline in their cognitive function during participation. Where there are concerns about a participants ability to provide ongoing consent, capacity will be assessed by an appropriately trained member of the research team in accordance with the Mental Capacity Act 2005 [48]. If required, a personal consultee will be approached to provide advice about their continued participation [48]. This will usually be a family member or close friend and may be the person acting as the nominated supporter. Where a personal consultee is not available, a nominated consultee may be identified and approached. They will be provided with a consultee information sheet and asked for their advice about whether the participant would want to continue in the trial. If the consultee advises that the participant would wish to continue in the trial, they will be asked to complete a consultee declaration form; otherwise, the participant will be withdrawn.

### Baseline assessments

Once participants have provided consent to take part in the trial, they will be asked to complete baseline questionnaires on the website (see Fig. 1 and ‘Primary outcome’ and ‘Secondary outcomes’ sections for details). An email link will take participants directly to the questionnaires and their responses will be automatically saved to the TIPTOE REDCap database repository. For participants who are unable or unwilling to complete the baseline measures on the trial website, the central trial team will contact via telephone to complete the baseline measures with the participant verbally.

### Randomisation method and implementation

Following completion of the baseline measures, participants will be individually allocated in a 1:1 ratio to the TIPTOE intervention or usual care arm using a minimisation algorithm with a random element [49]. Minimisation is based upon self-reported gender (male, female or other), OA site (knee, hip or both) and trial site. Participants and allocated sites will receive email notification informing them of which arm the participant has been randomised to.

### Follow-up

At 6 and 12 months post-randomisation, all participants will receive an email reminder requesting them to complete a selection of the questionnaires they completed at baseline (see Fig. 2). All participants who have completed both their 6- and 12-month follow-ups will be eligible to be entered into a prize draw for vouchers worth £100 with a 1 in 20 chance of receiving the incentive. There will be 2 draws.

### Activity monitoring

At baseline and 12-month follow-up, participants will be asked to wear an activity monitor (ActivPAL) on their thigh for 7 days and 7 nights to obtain an assessment of their physical activity. The ActivPAL4 device provides measures for a range of metrics including step count and time spent lying, sitting and standing. The device is covered in a nitrile sleeve and attached to the front of the participant’s thigh using a piece of Tegaderm®. The device will be posted to the participant by the central trial team. A demonstration video and instructions will be accessible on the TIPTOE website, explaining how to fit the device, what to do if they have any problems with the device and how to contact the trial team if support is required. Following the 7 days and nights, participants will be asked to return the device to the central trial team by posting via pre-arranged services. Data will be downloaded by the central trial team using the ActivPAL docking station and ActivPAL software and saved on a secure research drive. No identifiable data will be stored or collected by the ActivPAL devices.

## Process evaluation

In accordance with Medical Research Council guidelines for the development and evaluation of complex interventions [50, 51], an embedded mixed methods process evaluation will be conducted to explore trial process, intervention mechanisms and context, to inform future implementation of the TIPTOE intervention. The mixed methods process evaluation will be performed across three phases.

During the pilot phase of the trial, site staff from each region will be invited to take part in semi-structured interviews remotely. The aim of these interviews is to evaluate training and trial processes and potential sources for contamination between the intervention and control arms in trial delivery. Thematic analysis and rapid qualitative review will be used to feedback to the trial team and trial management group (TMG) to inform the main trial.

During the main phase of the trial, semi-structured interviews will be conducted with a subset of participants receiving the TIPTOE intervention (*n* =  ~ 20) and those receiving usual care (*n* =  ~ 5). Participants will be interviewed at baseline and post-intervention. We will aim to interview the same participants at both time points where possible. We will seek additional participants post-intervention, if it is not possible to interview the same participants from baseline. We will do this through sending out email reminders and highlighting the need for more interviewees on the monthly newsletter. Baseline interviews with participants receiving the TIPTOE intervention will aim to capture descriptions of usual care, contextual background (i.e. health experiences) and issues around the acceptability of the intervention (i.e. early perceptions, concerns, etc.). Baseline interviews with participants in the usual care group will also aim to capture descriptions of usual care as well as their experiences of trial processes (i.e. randomisation, recruitment, etc.). Post-intervention interviews with participants who received the TIPTOE intervention will aim to explore the acceptability of the intervention, adherence (did patients adhere to the intervention, did they alter it at all), advantages and disadvantages to the intervention, and barriers and facilitators to the intervention. Post-intervention interviews with the usual care participants will aim to explore if there have been any changes to their usual care and health experiences.

During the main phase of the trial, semi-structured interviews will also be conducted with healthcare practitioners (*n* =  ~ 20) who have been delivering the TIPTOE intervention. The interview guide will be based on domains from the updated Consolidated Framework for Implementation Research which acknowledges complex interactions between constructs that are associated with effective implementation [52]. We will purposefully sample for maximum variation across regions and across professional background (e.g. occupational therapists, physiotherapists, podiatrists, dietitians, pharmacists, nurses). The interviews will explore professionals’ views on acceptability (their views on the advantages and disadvantages of the intervention, barriers and facilitators to implementing the intervention, their perceptions on patients’ views on the intervention), adherence (their perceptions of whether patients adhered to the intervention, whether they made local changes) and adaptation (did the intervention work for this population group, did the healthcare practitioner have experience of using Bridges before the trial), reflections on training needs (was the training sufficient, how could it be improved) as well as trial processes (recruitment, randomisation, consent processes, patient materials, communication with the trial team).

Each healthcare practitioner delivering the intervention will be observed according to pre-determined quality markers which have been derived from previous research and co-design stages. They will be required to send in an audio or filmed recording of three of their intervention sessions. Feedback on their use of language which aligns with fidelity criteria will be provided by the Bridges team (who will have delivered training).

### Internal pilot

An internal pilot will be carried out from the start of recruitment and assessed after 6 months using a traffic light system [53, 54]. Green will result in the trial continuing as planned, amber will result in the trial continuing with changes, and red will result in the trial stopping.

### Study Within A Project (SWAP)

The SWAP will build on existing knowledge around the inclusion of older people [16, 42], people with impaired capacity to consent [17] and other under-served groups [18]. A mixed methods approach will be used to explore the methodological and systemic barriers to including older people with MLTCs in the trial through three phases.

During the pre-trial phase, we will establish the characteristics of the clinical population(s). Using a process mapping approach [55], we will work collaboratively with sites to map recruitment pathways to local care pathways with a focus on barriers to the inclusion of groups who are identified as under-served in this context, e.g. people with MLTCs, ‘oldest old’ and those with cognitive impairment, and other intersecting factors such as people from ethnic minority groups, people living in remote areas and those who are socioeconomically disadvantaged.

During the pilot phase of the trial, we will explore the attitudes, skills and confidence of research team members in recruiting participants from populations that are under-served through a series of one-to-one interviews (*n* =  ~ 10).

From this, we will transition from the pilot into the main phase of the trial using the SEAR (Screened, Eligible, Approached, Randomised) framework which aims to improve the process of recruitment to randomised controlled trials [56]. We will examine the proportion of people from under-served groups who were screened, identified as eligible and recruited to the trial, together with follow-up and retention rates. We will carry out one-to-one interviews with participants from under-served groups and their carers or supporters (*n* =  ~ 15, 10 from intervention arm and 5 from usual care arm) to explore their experiences of participating in the trial. Participants will be purposively sampled to reflect diversity, such as those population characteristics noted in the pre-trial mapping phase. This may include situations where a participant’s cognitive function affected their ability to engage (or remain engaged) with the intervention, and the feasibility of increasing support or providing an alternative option such as a supported form of self-management (a version of which is currently under development by the research team as ‘SUSTAIN’) [57].

Transcripts will be analysed through inductive thematic analysis informed by the findings from the previous phase. We will use a systems-based approach [58] to triangulate the findings with previous phases to identify barriers to the inclusion of people from under-served populations at either an individual, recruiter/site or trial level. Facilitative strategies will then be designed for rapid implementation during the main trial.

### Statistical analysis

Participant characteristics and baseline data will be summarised descriptively by allocation (intervention or usual care). Data analysts will be blinded to treatment group. The primary analysis will be intention-to-treat (i.e. all randomised participants, regardless of level of adherence to the allocated intervention or ‘contamination’ of usual care, with complete or incomplete follow-up, will be included), and use a partially clustered multi-level model, i.e. a linear mixed-effects regression model with an unstructured covariance structure imposed on the residuals to model the covariance between repeated measures on the same participant [59], and random cluster effects in the intervention arm to account for groups of participants receiving the intervention from the same healthcare team, allowing for heteroskedastic individual-level errors [60]. The model will include categorical time, treatment and their interaction as fixed effects, as well as any factors used to balance the randomisation in the minimisation algorithm. Baseline MSK-HQ will be included in the response variable. This model will be used to compare the mean MSK-HQ scores across follow-up time points between participants receiving the TIPTOE intervention and those receiving usual care using appropriate linear contrasts and a Kenward-Roger approximation to the denominator degrees of freedom [61]. Results will be presented as point estimates alongside two-sided 95% confidence intervals (CIs) and *p* values, as well as variance components and ICCs for healthcare team clustering. Clinical effectiveness will be concluded if the point estimate of the treatment effect favours the intervention, and the 95% CI excludes zero. Similar analyses will be performed for the secondary outcomes.

In secondary analyses, we will estimate the treatment effect at 6- and 12-month follow-up separately based upon the primary analysis model. We will also assess a potential difference in trend over time between the two arms. The primary analysis will be repeated with a random coefficients model using random effects for each participant’s intercept (and possibly slope) instead of the covariance pattern model described above. A per-protocol or complier average causal effect (CACE) analysis will explore the effect of treatment adherence whilst maintaining groups as randomised. Multiple imputation will be considered as a sensitivity analysis if warranted by the proportion of missing follow-up data. Other sensitivity analysis, such as modelling the outcome variable at baseline as a fixed-effects covariate and fitting a residual correlation structure that is stratified by treatment arm, will be considered. Planned subgroup analyses will involve stratification by (1) type of usual care provided at sites, (2) level of fidelity to the intervention, (3) mode of completion of outcome measures (self-reported versus proxy) and (4) number and type of long-term conditions. Safety outcomes will be tabulated by arm and analysed using logistic regression as appropriate. A comprehensive statistical analysis plan (SAP) will be agreed and signed off prior to database lock. Findings will be reported according to the Consolidated Standards of Reporting Trials (CONSORT) statement [62].

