### Sample size

The TIPTOE trial aims to recruit a total of 824 individuals with knee and/or hip OA and MLTCs. We aim to detect a minimum clinically important difference (MCID) of 0.3 standard deviations (SDs) between the randomised arms in the primary outcome of the MSK-HQ with 90% power whilst controlling the two-sided type 1 error level at 5%. This effect size is consistent with previous research where MCIDs of 0.3 SDs or greater were established for different pain sites [33]. An individually randomised trial with a normally distributed endpoint measured at a single follow-up time point would require 470 participants. Power in repeated measures designs, however, depends on additional factors such as the correlation between repeated measurements [40]: with non-zero correlation the power of a test for mean treatment difference between arms across follow-up time points in a mixed-effects regression model for repeated measures will exceed the power of a two-sample design if the effect size remains the same (0.3 SDs) across follow-up. The latter is unlikely in this study where the difference between arms might ‘peak’ around the time the intervention programme ends and not be fully sustained at 12 months, or conversely, where the full effect might not yet have become manifested at 6 months. Using GLIMMPSE (University of Colorado, Denver, USA) version 3.0.0 with calculations based on the Hotelling-Lawley trace test, which is equivalent to a mixed-model test [41], we studied the power of designs with *n* = 470 under a range of plausible scenarios involving first-order autoregressive correlation structures over time with parameter rho between 0.3 and 0.7 and treatment effects at least the size of the MCID at least at one follow-up time point whilst assuming no difference between treatment arms at baseline due to randomisation. The power exceeded 90% for most of these scenarios and never fell below 83.5%. For most scenarios, between 70 and 90% power was also achieved for testing differences in trend over time between arms.

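### The primary model takes baseline MSK-HQ as a response but leaves each arm's baseline mean free, so the follow-up contrast gives up precision that equal baseline means would supply

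*Protocol article*

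**What the plan says.** In the protocol article, under Statistical analysis, the primary analysis is a linear mixed model with unstructured residual covariance and team random effects in the intervention arm. Its mean structure is stated: "The model will include categorical time, treatment and their interaction as fixed effects, as well as any factors used to balance the randomisation". The next sentence reads "Baseline MSK-HQ will be included in the response variable". The primary comparison is of mean MSK-HQ over the follow-up time points, by linear contrast. No constraint of equal arm means at baseline is stated.

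The baseline-adjusted alternative, "modelling the outcome variable at baseline as a fixed-effects covariate", appears later in that section, among sensitivity analyses to be considered.

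The Sample size section did its repeated-measures power work "whilst assuming no difference between treatment arms at baseline due to randomisation", using "first-order autoregressive correlation structures over time with parameter rho between 0.3 and 0.7".

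**The concern.** A treatment main effect, categorical time and their interaction, fitted to a response that includes baseline, give six free means: two arms at three times. The baseline difference between arms becomes a parameter to be estimated, although randomisation makes its true value zero. With a saturated mean structure, unstructured covariance and complete data, the fitted follow-up difference is the raw difference in observed follow-up means. The baseline score, collected before randomisation and correlated with the outcome, then adds nothing to the estimate.

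Two things are at stake. The confidence interval is wider than it need be, and a chance imbalance in baseline MSK-HQ carries into the reported effect. The minimisation factors (gender, OA site, trial site) do not include baseline MSK-HQ, so the design does not limit that imbalance either. Secondary outcomes measured at baseline are affected too, because they are to be analysed in a similar way.

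**Working it through.** **Inputs.** From Sample size: "minimum clinically important difference (MCID) of 0.3 standard deviations (SDs) between the randomised arms", "with 90% power whilst controlling the two-sided type 1 error level at 5"%, AR(1) correlation with rho 0.3 to 0.7, ICC 0.02 in the intervention arm, 16 teams averaging 18, 576 analysed, 30% loss, 824 recruited. My assumptions: SD 1 at each visit; losses miss both follow-ups, equally in the two arms and at random; minimisation factors ignored.

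**The plan's own figures first.** The article says that a trial "measured at a single follow-up time point would require 470 participants". A two-sample t-test with 235 per arm has 90.07% power at 0.3 SD, so 470 reproduces. The 83.5% power floor also reproduces without baseline adjustment. For a 2-df test of the two follow-up differences, with one of them at 0.3, noncentrality is smallest when the other is rho × 0.3. It then equals (470/4) × 0.3² = 10.575 for any rho, which gives 83.5% power. The contrast of follow-up means, also unadjusted, gives 83.5% with effects of 0.3 and 0.2 at rho 0.7. The article does not list its effect patterns, so I cannot say which it used. Neither calculation needs baseline adjustment.

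**Variance of the follow-up mean (complete data, no team effect).**
- Free baseline means: v = (1 + rho)/2.
- Covariance of baseline with the follow-up mean: c = (rho + rho²)/2.
- Equal baseline means: a = v − c².

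| rho | v | c | a | v/a |
|---|---|---|---|---|
| 0.3 | 0.650 | 0.195 | 0.612 | 1.06 |
| 0.5 | 0.750 | 0.375 | 0.609 | 1.23 |
| 0.7 | 0.850 | 0.595 | 0.496 | 1.71 |

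**With 30% lost at both follow-ups.** Per arm and per participant recruited, the variance is a/0.7 + c² with free baseline means and a/0.7 with equal ones. The ratio is 1 + 0.7c²/a:
- rho 0.3: 1 + 0.7 × 0.038/0.612 = 1.04
- rho 0.5: 1 + 0.7 × 0.141/0.609 = 1.16
- rho 0.7: 1 + 0.7 × 0.354/0.496 = 1.50

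**With 30% loss and ICC 0.02 acting only after baseline.** Take 412 recruited per arm over 16 teams. The team effect adds 0.02 × 412/16 = 0.515 to both variances on this scale, so the ratio is [2(a/0.7 + c²) + 0.515]/[2a/0.7 + 0.515]:
- rho 0.3: 2.340/2.264 = 1.03
- rho 0.5: 2.537/2.256 = 1.12
- rho 0.7: 2.640/1.932 = 1.37

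Generalised least squares on the full models agrees to within rounding at rho 0.3 and 0.5, and gives 1.36 to 1.37 at rho 0.7.

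**Chance imbalance.** With complete data, a baseline difference d shifts the expected follow-up contrast by c × d. With 288 per arm, one standard error of d is √(2/288) = 0.083 SD. The shift is then 0.016, 0.031 or 0.050 SD at rho 0.3, 0.5 or 0.7, against a target of 0.3.

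**Power** (normal approximation; 288 complete per arm; 16 teams; ICC 0.02; variance (2v + 0.36)/288 or (2a + 0.36)/288, where 0.36 = 0.02 × 288/16).

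| Effects at the two follow-ups | Model | rho 0.3 | rho 0.5 | rho 0.7 |
|---|---|---|---|---|
| 0.3 and 0.3 | free baseline | 0.98 | 0.96 | 0.94 |
| 0.3 and 0.3 | equal baseline | 0.98 | 0.98 | 0.99 |
| 0.3 and 0.2 | free baseline | 0.91 | 0.88 | 0.84 |
| 0.3 and 0.2 | equal baseline | 0.92 | 0.92 | 0.95 |

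The 0.2 is illustrative. The article says only that the effect may not be equal at both times.

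**The case against.** The strongest reply is that the stated model is valid and the trial was sized for it. That stands. The estimate is unbiased, type I error is controlled, and 470 and 83.5% both come out of unadjusted variances. A reader might infer that the trial is underpowered as a result, but the documents do not support this: a sustained 0.3 SD effect leaves power above 90% under either model. Nor does the power work's assumption of equal arms at baseline contradict the model. It describes the true means in the scenarios; the model merely makes no use of it.

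A reader might also take 71% as the size of the problem, or as 71% more participants. That figure needs rho at the top of the range, no missing data and no team effect, whereas the plan expects 30% loss and an ICC of 0.02. Adding participants to the same 16 teams would not shrink the team component either. Nor is baseline wholly unused: where follow-up is missing, the unstructured covariance brings some of it in.

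In the other direction, the excess would be 16%/34%/78% (with 30% loss) if team effects were also present at baseline. The article attributes this clustering to delivery of the intervention, which has not begun at baseline, so I do not rely on those figures.

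Finally, the article is condensed and the SAP is not shown; it could add the constraint. But the article does state the fixed effects, and a constrained SAP would depart from them. Leaving the comparison to suitable linear contrasts does not help, because a contrast cannot restore a constraint that the model lacks.

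**Conclusion.** The point holds as one of efficiency. As written, the primary contrast has about 3%/12%/37% more variance than an equal-baseline model at rho 0.3/0.5/0.7 under the plan's 30% loss and an ICC of 0.02 acting after baseline. The excess is 4%/16%/50% with the loss alone and 6%/23%/71% with complete data and no team effect. These figures rest on AR(1) correlation, equal variances over time and loss at both follow-ups. The gain is slight at low correlation and material at moderate to high correlation. What it does for power depends on the assumed effects: little if 0.3 SD is sustained, more if the effect is uneven. Validity and the planned sample size are not in question.

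**What to change.** In Statistical analysis, replace the treatment main effect and full interaction with categorical time plus treatment-by-time terms at 6 and 12 months only, so that the arm means are constrained to be equal at baseline. State that the intervention-arm team random effects act only on the 6- and 12-month responses; without this the constrained model is not fully specified. Keep the unstructured covariance and the minimisation factors. Define the primary contrast as the average of the 6- and 12-month treatment terms. Every randomised participant with a baseline score stays in the model.

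The cost is a short change to the protocol and SAP wording and to the model code, with some care over coding the team effect. No new data are needed. Fix it before database lock, so that the choice between adjusted and unadjusted estimates cannot be influenced by the results.

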### Fidelity of TIPTOE intervention delivery

To assess intervention fidelity, healthcare practitioners will complete a pre-post training questionnaire addressing their knowledge, skills and confidence on a 3-point Likert scale covering a range of items relating to the key principles of Bridges Self-management and contextualised to the delivery of the TIPTOE intervention. Additionally, healthcare practitioners will be asked to audio record three coaching sessions, which will be evaluated against an adapted pre-existing fidelity checklist for the key attributes they are expected to demonstrate during intervention delivery [31]. Participants will be made aware if their session will need to be recorded, and each recording will be stored in a secure space only accessible by the trial team and TIPTOE practitioner. Reflections from the practitioners delivering the intervention will be captured through online notes pages, completed after each participant session, only accessible by the TIPTOE practitioner and the central trial team.

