### Usual care

All participants randomised to the control arm will continue to receive their usual care as currently available in the NHS within the participant’s region and services. Usual care for OA typically involves pathology specific assessments and treatment services with individuals with OA being offered a combination of core treatments such as exercise, weight management, self-management education and advice. This may be on an individual or group basis in primary, secondary or community care. We will record the usual care received by completing a bespoke Client Services Receipt Inventory (CSRI) at baseline and 6 and 12 months post-randomisation, in both arms. We will also focus on exploring usual care as part of the mixed methods process evaluation.

Participants in the control group will receive the co-designed Living Well book following completion of their 12-month follow-up.

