## Outcomes

### Primary outcome

The primary outcome measures are symptoms and QoL, assessed on the Musculoskeletal Health Questionnaire (MSK-HQ). The MSK-HQ is a 14-item scale which measures the holistic effect of MSK pain on symptoms and health-related QoL. The MSK-HQ has been shown to be both valid and reliable [32, 33]. It will be measured at baseline, 6 months (end of intervention) and 12 months (to assess in a repeated measures analysis if the intervention has a sustained effect).

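### Level of fidelity is listed as a subgroup stratifier, but it arises after randomisation and has no value in the usual-care arm; mode of completion is a valid subgroup only if fixed at baseline

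*Protocol article*

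**What the plan says.** The Statistical analysis section introduces the list with "Planned subgroup analyses will involve stratification by" and names four stratifiers: type of usual care at sites, fidelity, mode of completion, and number and type of long-term conditions. The second and third read "2) level of fidelity to the intervention, (3) mode of completion of outcome measures (self-reported versus proxy".

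On how fidelity is obtained, the section on fidelity of intervention delivery states that "healthcare practitioners will be asked to audio record three coaching sessions, which will be evaluated against an adapted pre-existing fidelity checklist". The Process evaluation section adds that "Each healthcare practitioner delivering the intervention will be observed according to pre-determined quality markers". On the comparator, the Usual care section states that "All participants randomised to the control arm will continue to receive their usual care as currently available in the NHS".

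On timing, the Primary outcome section says of the MSK-HQ: "It will be measured at baseline, 6 months (end of intervention) and 12 months". The randomisation section places allocation after the baseline measures.

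The Statistical analysis section also plans a per-protocol or complier average causal effect (CACE) analysis that keeps the groups as randomised. It is described for treatment adherence. Fidelity is not mentioned there.

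**The concern.** A subgroup analysis gives a treatment effect because, within each level of a characteristic fixed before allocation, randomised participants are compared with randomised participants. Fidelity does not meet that condition. It describes how a practitioner delivered the coaching, becomes known only after allocation, and is undefined for anyone in usual care. An analyst following the text at practitioner or participant level must either leave the stratum without controls or set a selected part of the intervention arm against all controls. The second option looks like a subgroup effect but is a non-randomised comparison. Differences between teams and their case mix can appear as an effect of good delivery.

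At stake is how a finding such as a larger effect with high fidelity would be read. The Qualitative analysis section plans to combine the quantitative fidelity results with the qualitative findings in order to understand mechanisms and support implementation after the trial.

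Mode of completion raises a related but weaker question. If the mode used at 6 or 12 months defines the strata, membership could depend on what happened after allocation.

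**Working it through.** **1. Is each stratifier fixed before allocation and defined in both arms?**

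| Stratifier | When it arises | Defined in usual care? |
|---|---|---|
| Type of usual care at sites | Site attribute | Yes, worded at site level |
| Level of fidelity | After allocation, from recorded sessions, per practitioner | No, there are no sessions |
| Mode of completion | Baseline, 6 and 12 months; time point not stated | Yes, but pre-randomisation only at baseline |
| Number and type of conditions | Participant attribute; comorbidity is assessed for eligibility | Yes |

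Only fidelity has no value in the control arm. An ordinary arm-by-fidelity interaction cannot be estimated, because one arm has no variation in the variable and indeed no value of it.

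One reading would keep randomisation intact: a fidelity score per site, given to both arms. Trial site is a minimisation factor, so comparisons within a site remain randomised. The text does not say this. The first item is worded as being at sites and the second is not, and ratings are made per practitioner.

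**2. The plan's own figures.** The subgroup analyses have no stated figure. The sample size, from which the group sizes below are taken, reproduces:
- 0.3 SD, 90% power, two-sided 5%, two-sample t-test: 235 per arm, 470 in total, as stated.
- Partial clustering: design effect in the intervention arm 1 + (18 − 1) × 0.02 = 1.34. Per arm, (1.960 + 1.282)² × (1 + 1.34) / 0.3² = 273.2. In teams of 18 this needs 16 teams, so 16 × 18 = 288 per arm and 576 in total, as stated.
- 30% loss: 288 / 0.7 = 411.4, rounded up to 412; 2 × 412 = 824, as stated.

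**3. Size of a possible fidelity bias (assumptions, not in the documents).** If the high-fidelity group has a prognosis better than the controls by δ and there is no true effect, the apparent effect is δ. For δ = 0.1 SD this is 0.1 / 0.3 = one third of the minimum clinically important difference; for δ = 0.2 SD it is two thirds.

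The same idea in terms of a correlation r between fidelity and participant prognosis: compare the upper half of the intervention arm (144) with all 288 controls, true effect zero, clustering ignored. The bias is r × 0.399 / 0.5 and the standard error is √(1/144 + 1/288) = 0.102 SD.

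| r | Spurious effect (SD) | Share of 0.3 SD | False-positive rate |
|---|---|---|---|
| 0 | 0 | 0% | 5% |
| 0.1 | 0.08 | 27% | 12% |
| 0.2 | 0.16 | 53% | 35% |
| 0.3 | 0.24 | 80% | 65% |

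A negative correlation would give a bias of the same size in the other direction.

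**4. Size of a possible mode bias if follow-up mode were used (assumptions).** Let proxy completion occur below a cut-off on a health trait that has correlation g with the outcome, with no true effect. With proportion p using a proxy and φ the normal density at the cut-off, the mean outcome is −gφ/p in the proxy stratum and gφ/(1 − p) in the self-report stratum. With 20% proxy in controls, 15% or 10% in the intervention arm, and g from 0.3 to 0.5, the spurious difference is −0.05 to −0.18 SD in the proxy stratum and −0.02 to −0.08 SD in the self-report stratum. If both arms have 20% proxy with the same selection, or if mode is fixed at baseline, it is zero.

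**The case against.** The strongest reply is that these are additional analyses. Effectiveness is concluded from the primary intention-to-treat contrast alone, and a full statistical analysis plan is to be signed off before database lock. That stands, and it limits the severity. It does not remove the fidelity point, because the issue is not missing detail: the article names an intervention-only variable as a planned subgroup, and a plan that follows it would carry the problem over.

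A second reply is that the primary model includes the minimisation factors, so if the subgroup analyses use that model, differences between sites are adjusted for. This also stands. Differences between teams and in case mix within a site would remain.

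Third, the documents give no figure for a link between fidelity and prognosis. That is correct, and the sizes above are only illustrations.

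On mode of completion, a reader might infer that this subgroup is invalid too. The documents do not support that. Outcome measures are also completed at baseline, before randomisation, and the time point that defines the subgroup is left open. Nor do they show that proxy use would differ by arm. A nominated supporter is encouraged for trial participants generally; only joining coaching sessions is specific to the intervention. The possible cognitive decline noted in the consent section could occur in either arm.

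A reader might also take the words on stratification to rule out interaction tests. They do not, and the choice of test can be left to the analysis plan.

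**Conclusion.** The point holds for fidelity at practitioner or participant level: as listed, it cannot give a randomised treatment effect. This follows from the text and rests on no numerical assumption. For mode of completion it holds only conditionally, if follow-up mode were to define the strata.

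The size and direction of any bias are unknown. The figure of one third to two thirds of the 0.3 SD difference rests on an assumed prognostic gap of 0.1 to 0.2 SD, and with no gap there is no bias. It would be wrong to infer that the trial's main conclusion is threatened: the primary analysis and the target of 824 are untouched. Severity is moderate.

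**What to change.** - **Fidelity.** Remove item (2) from the subgroup list and report it as an association within the intervention arm, labelled explicitly as non-randomised. Alternatively, score fidelity by site, attach the score to both arms and test its interaction with arm. State with this option that about 8 expected sites make the test imprecise, and that Wales counts as one site covering seven Health Boards, so its single score would average over different teams.
- **Mode of completion.** Define item (3) by mode at baseline and keep follow-up mode descriptive. First confirm that self-report or proxy status is recorded at baseline, since the article does not say so.

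The cost is a change of wording in the protocol or the analysis plan before database lock. The within-arm fidelity analysis uses ratings that are already planned. The only possible extra work is recording mode at baseline if this is not already done, and the article describes recruitment as still open.
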